### Characteristics and health status of each group

2.12

In order to verify whether or not statistical differences in characteristics and/or health status exist among treatment group 1, treatment group 2, and the control group, we will calculate the average, standard deviation, minimum value and maximum value for continuous data, and we will compare the average values for the three groups by using the t-test. For the purpose of group comparisons, we will use the chi-squared test or Fisher's exact test for categorical data.

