### Analysis of second outcome variables

2.14

Descriptive statistics (number in each group, average, standard deviation, minimum value and maximum value) will be used to describe differences in the CR, PR, SD, PFS, TTP, tumor marker (CEA, NSE), WBC differential count (LMR, NLR), natural killer cell activity and QOL (EORTC QLQ-C30) between the two test groups and the control, and any differences between either of the two test groups and the control at the last visit versus baseline will be presented. The statistical significance of any difference found between test groups and the placebo group will be analyzed using chi squared test. If any difference among three groups (2 test groups and 1 placebo group) exist, Bonferroni or Duncan method will be used. Chi squared test between placebo group and treatment group 1, placebo group and treatment group 2 will be additionally conducted. The statistical significance of any variable in any group will be tested by using the paired *t* test or the Wilcoxon signed rank test.

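### Section 2.14 names the chi-squared test as the between-arm test for every secondary outcome, but it does not suit the time-to-event outcomes (PFS, TTP) or the continuous ones

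*Protocol article*

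**What the plan says.** Section 2.14 (analysis of second outcome variables) treats all secondary outcomes together. Summary statistics (mean, SD, minimum, maximum) are to "describe differences in the CR, PR, SD, PFS, TTP, tumor marker (CEA, NSE), WBC differential count (LMR, NLR), natural killer cell activity and QOL".

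One testing rule then follows for the whole list:

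- Overall comparison: "The statistical significance of any difference found between test groups and the placebo group will be analyzed using chi squared test".
- Follow-up: "If any difference among three groups (2 test groups and 1 placebo group) exist, Bonferroni or Duncan method will be used".
- Each dose against placebo: "Chi squared test between placebo group and treatment group 1, placebo group and treatment group 2 will be additionally conducted".
- Within each arm: "The statistical significance of any variable in any group will be tested by using the paired" t test or the Wilcoxon signed rank test.

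The overall-test sentence also appears word for word in section 2.13, where the outcome is the DCR.

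Section 2.12, on baseline characteristics, does separate data types. It assigns chi-squared or Fisher's exact test to categorical data, and for continuous data it says "we will compare the average values for the three groups by using the t-test".

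**The concern.** A Pearson chi-squared test compares counts across categories. It uses neither the order of measured values nor the distance between them, and it has no way to handle a patient whose progression time is censored. Eight of the eleven listed outcomes (PFS, TTP, CEA, NSE, LMR, NLR, NK activity, QLQ-C30) are times, measurements or scores.

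This is not a detail left to an unseen analysis plan. A specific test is named, once for the overall comparison and again for the pairwise ones, and it is the wrong kind of test for most of the list. It also departs from the categorical/continuous distinction that section 2.12 draws.

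The only tests in section 2.14 named outright that suit continuous data are the paired ones, and these compare an arm with its own baseline. Section 2.5 gives afatinib to all three arms, so a change within one arm cannot be credited to HAD-B1. PFS and TTP have no baseline value to pair.

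At stake is whether the tumour-marker, immune, quality-of-life and progression-time results rest on a pre-stated between-arm comparison, or on a method chosen later by whoever finds that the stated one does not work.

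**Working it through.** **Inputs.** Section 2.1: three arms, 1:1:1, 12 weeks of treatment. Section 2.9: 15 patients per arm needed, 30% dropout. Section 3 (Discussion): median PFS of 9–12 months on EGFR-TKIs. Effect sizes and distributions below are assumptions, because the article gives none.

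**The plan's own figure.** 15/(1 − 0.3) = 21.43, rounded up to 22 per arm; 3 × 22 = 66. This reproduces. The point does not depend on it, but it gives the two sizes to use: 22 per arm enrolled and 15 evaluable.

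**1. Chi-squared taken literally on continuous values.** With k equal arms and N distinct values, each value is its own column with one patient in it. The expected count in every cell is 1/k. Each column contributes

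k(1 − 1/k)² + (k − 1)/k = k − 1,

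so the statistic is N(k − 1) on (N − 1)(k − 1) df, whatever the values are.

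| Arms × n | Statistic | df | p |
|---|---|---|---|
| 3 × 22 | 66 × 2 = 132 | 65 × 2 = 130 | 0.43 |
| 3 × 15 | 45 × 2 = 90 | 44 × 2 = 88 | 0.42 |
| 2 × 22 | 44 | 43 | 0.43 |
| 2 × 15 | 30 | 29 | 0.41 |

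Simulated data with true shifts of 0, 1 and 10 SD in the dose arms gave exactly these results each time. For one simulated data set per shift at 3 × 22, a one-way ANOVA gave p = 0.77, 0.016 and about 4 × 10⁻⁴⁵.

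Tied values, as QLQ-C30 will have, loosen the exact constancy but do not repair the test. A score shared by m patients has an expected count of m/3 per arm, so an expected count of 5 needs 15 patients on the same score, and the scores are still treated as unordered.

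**2. Chi-squared after dichotomising (not stated in the article).** For an assumed median split of normal data, large-sample efficiency relative to comparing means is 2/π = 0.637. This equates to 0.637 × 22 = 14.0 of 22 patients, or 0.637 × 15 = 9.6 of 15. Simulated power for two arms, two-sided 0.05:

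| Assumed difference | n per arm | t-test | Median split, chi-squared |
|---|---|---|---|
| 0.8 SD | 15 | 56% | 32% |
| 0.8 SD | 22 | 73% | 49% |
| 1.0 SD | 15 | 75% | 47% |
| 1.0 SD | 22 | 90% | 68% |

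**3. PFS and TTP.** Assume exponential times and follow-up to 12 weeks (84/30.4375 = 2.76 months). The share progressed is 1 − 2^(−2.76/median): 19.1% at a median of 9 months and 14.7% at 12 months. That is about 7 to 9 of 45 patients, or 10 to 13 of 66. More than 80% of times would be censored. A contingency table cannot represent that, and a plain mean and SD of such times describe mainly the follow-up.

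**The case against.** **The chi-squared test is not the only procedure named.** Duncan's method compares means, which hints at an ANOVA that was intended but not written. This stands as a qualification. The follow-up applies only if a difference has already been found, no ANOVA precedes it, and it does not fit PFS or TTP, so chi-squared remains the test that everything depends on.

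**The sentence may simply have been carried over from section 2.13.** That is plausible, since the wording is identical. It explains the error without correcting it, and no other section overrides it.

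**A reader might infer that all these secondary results would be invalid.** The document does not support that. Chi-squared suits CR, PR and SD, subject to small expected counts. A dichotomised marker, or progression status at 12 weeks with complete follow-up, would give a valid though wasteful test. The accurate description is unsuitable as written.

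**A reader might also infer that PFS will be cut to yes/no at 12 weeks and so merely repeat the DCR comparison, or that within-arm changes will be presented as HAD-B1 effects.** The article states neither. It gives no cut for PFS and draws no HAD-B1 conclusion from the paired tests, which are acceptable as description.

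**Survival methods will gain little here.** This is partly right. Under the assumptions above, a dose-versus-placebo comparison would have about 4 to 6 events in 30 patients (30 × 0.147 = 4.4; 30 × 0.191 = 5.7) or 6 to 8 in 44 (44 × 0.147 = 6.5; 44 × 0.191 = 8.4). Hazard ratios would be very imprecise. That calls for cautious reporting and does not justify a test that ignores censoring.

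**Conclusion.** The point holds as a wrong test stated for most of the secondary list. Section 2.14 leaves PFS, TTP, CEA, NSE, LMR, NLR, NK activity and QLQ-C30 without a usable primary between-arm test.

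The constancy of the literal chi-squared result is algebra and needs only equal arms and untied values. The 64% efficiency and the power figures assume normal data and a median split that the article does not propose; they show what one possible rescue would cost, not what the plan prescribes. The event counts assume exponential times, the quoted medians and follow-up ending at 12 weeks.

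The reach is limited. The trial is exploratory, these are secondary outcomes, and the primary DCR comparison in section 2.13 is categorical and unaffected.

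The t-test in section 2.12 is a minor, separate matter. A single t-test does not compare three means. Pairwise t-tests are a possible if loose reading, and only the baseline description is involved.

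**What to change.** Reword section 2.14 by outcome type, before unblinding:

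- **PFS and TTP:** Kaplan-Meier estimates and a log-rank test, with a Cox hazard ratio and 95% CI for each dose versus placebo. Add a note that few events are expected by 12 weeks.
- **CEA, NSE, LMR, NLR, NK activity, QLQ-C30:** a between-arm comparison adjusted for the baseline value (ANCOVA), or a rank test where the distribution is skewed, for each dose versus placebo.
- **Binary response outcomes:** keep chi-squared, or Fisher's exact test where expected counts are small, and restrict these tests to such outcomes.
- **Within-arm paired tests:** keep if wanted, labelled descriptive and not as evidence of a HAD-B1 effect.

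Separately, in section 2.12 replace the three-group t-test with ANOVA or Kruskal-Wallis, or report baseline characteristics descriptively.

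The cost is rewording two sections. No patients are added, and the week 6 and week 12 assessments in section 2.6 already supply the marker and questionnaire data. The changes do not make PFS or TTP precise; that would depend on follow-up beyond what section 2.6 describes.

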### Trial design

2.1

This study is a randomized, double-blinded, placebo-controlled trial that aims to examine the efficacy and safety of HAD-B1 for EGFR positive and locally advanced or metastatic NSCLC patients who need afatinib therapy. Also, the results will provide the proper dosage of HAD-B1 for the patients. Participants will be randomized using a ratio of 1:1:1 into treatment group 1 (afatinib 40 mg/day plus HAD-B1 2 tablets (972 mg/day) plus placebo 2 tablets, treatment group 2 (afatinib 40 mg/day plus HAD-B1 4 tablets [1944 mg]) and control group (afatinib 40 mg/day plus placebo 4 tablets). Afatinib combined with HAD-B1 or placebo will be administered to the participants for 12 weeks (Table 2).

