### Interventions

2.5

Patients in the treatment group 1 will receive afatinib (40 mg/day orally) plus HAD-B1 2 tablets (972 mg/day, bid orally) and placebo 2 tablets, those in the treatment group 2 will receive afatinib (40 mg/day orally) plus HAD-B1 4 tablets (1944 mg/day, bid orally), while those in the control group will receive afatinib (40 mg/day orally) plus placebo 4 tablets (bid orally). Afatinib, HAD-B1 and/or placebo will be administered consistently for 12 weeks; the trial may be terminated before the end of 12 weeks due to the development of unacceptable toxicities or withdrawal of the participant from the treatment.

The HAD-B1 tablets used in clinical trial will purchased from the Gyeongbang Pharmaceutical Co., Ltd. (In-cheon, Korean) and will meet the requirements of Good Manufacturing Practice (GMP). HAD-B1 is a medical substance that contains *Panax ginseng C.A.* (640 mg), *Panax notoginseng Radix* (839 mg), *Cordyceps militaris* (640 mg), and *Boswellia carterii BIRDWOOD* (480 mg) as raw material medicines is extracted for 16 hin purified water at 60°C. Then, the filtrate is concentrated under reduced pressure to obtain a dry extract of 486 mg. From this, 650 mg of one brown film-coated tablet is produced by adding excipients.^[10]^ The matching placebo will be purchased from the same manufacturer and consist of starch with no active ingredients.

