### Outcome measures

2.6

The primary outcome is a comparison of the disease control rates (DCR) among treatment groups 1 and 2 and the control group after 12 weeks compared to baseline, which will be assessed from the date of randomization to 12 weeks, as determined by chest X-ray, CT or MRI according to the RECIST criteria.^[11]^

The secondary outcomes are comparisons of the complete response (CR) and the partial response (PR) to the treatment, the stability of the disease (SD), progression free survival (PFS), time to progression (TTP), and tumor marker (CEA, NSE) and WBC differential count (LMR, NLR) and natural killer cell activity and QOL (EORTC QLQ-C30) among treatment groups 1 and 2 and the control group after 6 weeks and 12 weeks compared to baseline.

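### Paired within-arm tests of markers and QOL cannot isolate HAD-B1, because every arm takes afatinib, and the between-arm test named beside them does not suit continuous data

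*Protocol article*

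**What the plan says.** Section 2.6 lists among the secondary outcomes "tumor marker (CEA, NSE) and WBC differential count (LMR, NLR) and natural killer cell activity and QOL (EORTC QLQ-C30", to be compared "among treatment groups 1 and 2 and the control group after 6 weeks and 12 weeks compared to baseline".

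Section 2.14 plans two kinds of inference for these variables.

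- **Between arms.** It promises that "any differences between either of the two test groups and the control at the last visit versus baseline will be presented". It then states: "The statistical significance of any difference found between test groups and the placebo group will be analyzed using chi squared test". A Bonferroni or Duncan step follows if the three groups differ. Finally, "Chi squared test between placebo group and treatment group 1, placebo group and treatment group 2 will be additionally conducted".
- **Within arms.** The section closes with: "The statistical significance of any variable in any group will be tested by using the paired" t test or the Wilcoxon signed rank test.

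Afatinib 40 mg/day is common to all arms. Section 2.5 says that "those in the control group will receive afatinib (40 mg/day orally) plus placebo 4 tablets (bid orally"), and both HAD-B1 groups take the same afatinib regimen.

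**The concern.** A paired test asks whether the mean or median change inside one arm differs from zero. In a HAD-B1 arm that change contains whatever afatinib does, whatever happens over 12 weeks, regression to the mean, and any effect of HAD-B1. The trial's question is what HAD-B1 adds to afatinib, and only the contrast with the afatinib-plus-placebo arm answers it.

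The hazard is a familiar misreading: a change that is significant in a HAD-B1 arm but not in control is taken as a difference between arms. With two HAD-B1 arms and one control, the pattern has two chances to appear. With 15 to 22 patients per arm, arms that share the same true change will often fall on opposite sides of 0.05.

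The between-arm plan should guard against this, but the test it names works on counts in categories, not on continuous concentrations, ratios, activity values or questionnaire scores. The usable p-values for these outcomes are therefore likely to be the paired ones.

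**Working it through.** **Arm sizes (section 2.9).** 15/(1 − 0.3) = 21.43, rounded up to 22 per arm, and 3 × 22 = 66. The plan's figures reproduce. Both 15 (evaluable) and 22 (enrolled) per arm are used below.

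**Assumptions not in the documents.** Two-sided 0.05; normally distributed change scores; no HAD-B1 effect; and one shared change of d standard deviations (SD) of the change score in every arm. The documents give no size for this change, so d runs from 0 to 1.0.

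**Formula.** Let p be the power of the paired t test in one arm and q = 1 − p. The arms are independent, so

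P(at least one HAD-B1 arm significant, control not) = (1 − q²) × q = q − q³.

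| d (SD) | p, n=15 | q − q³, n=15 | p, n=22 | q − q³, n=22 |
|---|---|---|---|---|
| 0 | 0.05 | 9% | 0.05 | 9% |
| 0.3 | 0.19 | 28% | 0.27 | 34% |
| 0.4 | 0.30 | 36% | 0.43 | 38% |
| 0.5 | 0.44 | 38% | 0.61 | 33% |
| 0.6 | 0.58 | 35% | 0.77 | 22% |
| 0.8 | 0.827 | 17% | 0.946 | 5% |
| 1.0 | 0.948 | 5% | 0.994 | 1% |

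Worked example, n=15 and d=0.5: q = 0.56, and 0.56 − 0.56³ = 0.56 − 0.176 = 0.384.

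**Ceiling.** q − q³ is largest where 1 − 3q² = 0, that is q = 0.577 (power about 0.42). The maximum is 0.577 × 2/3 = 38.5%. No shift size can exceed this.

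**Simulation check.** 20,000 simulated trials per scenario, at d = 0, 0.3, 0.5, 0.8 and 1.0, gave 9.3%, 27.8%, 38.6%, 17.0% and 5.0% for n=15, and 8.9%, 33.8%, 33.4%, 5.1% and 0.6% for n=22. These agree with the formula within simulation error.

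**Between-arm comparison in the same simulated trials.** A two-sample test of change, each HAD-B1 arm against control, rejected in about 5% of trials per pair at every d. Either of the two pairs rejected in about 9% at 0.05 each, or about 4.5% at 0.025 each. The shared change cancels.

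**The case against.** The strongest reply is that section 2.14 is mainly a between-arm plan. It presents differences from control, tests against placebo, provides a multiplicity step and adds a pairwise test for each HAD-B1 group. Section 2.6 defines the secondary outcomes as comparisons among the three groups. The paired tests come last and can be read as supplementary, in a trial that calls itself exploratory. All of this stands.

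A reader might infer that the plan intends to credit within-arm significance to HAD-B1. No sentence says so. A reader might also infer that the choice between 972 and 1944 mg would rest on these p-values. The article says the trial will inform dosage but never ties that to paired tests of markers or QOL, and the primary outcome is DCR compared among groups.

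The size of the problem can be overstated too. The 0.3–0.6 SD range straddles the mathematical peak, and the pattern fades on both sides of it. Nor can it be called likely for at least one of the five blood markers. That would need every marker to lie in the unfavourable range and the tests to be independent, and LMR and NLR share the lymphocyte count. Even under independence, 9% per marker gives 1 − 0.91⁵ = 38%, and 1% gives 1 − 0.99⁵ = 5%.

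One part of the reply is weaker than it looks. Duncan's method does compare means, but it is named only as a follow-up once a difference among the groups is found, and the test named for finding one is chi-squared. The planned comparison with placebo therefore does not, as written, supply a sound check on the paired results.

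**Conclusion.** The point holds as a risk built into the stated analysis. The paired p-values cannot isolate HAD-B1 in a trial where every arm takes afatinib. They are also the only tests that section 2.14 names, apart from the conditional Duncan follow-up, that suit continuous markers and QOL scores.

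Under no HAD-B1 effect, the misleading pattern has a per-marker probability of about 9% with no shared change, at most 38.5% at intermediate changes, and 5% or less at 1.0 SD. Where an outcome falls in that range depends on a shift that the documents do not give. The figures also rest on normality and an assumed two-sided 0.05. The structural conclusion needs none of these assumptions: a within-arm test answers a different question from the trial's.

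**What to change.** In section 2.14:

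1. Report within-arm change for CEA, NSE, LMR, NLR, NK cell activity and QLQ-C30 descriptively with confidence intervals. If the paired tests are kept, label them descriptive only and say that a within-arm change is not evidence of HAD-B1 activity.
2. Base every statement about HAD-B1 on these outcomes on the difference in change between each HAD-B1 arm and afatinib plus placebo. Use a method for continuous data, such as ANCOVA with baseline as covariate, or a rank-based equivalent.

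This changes wording and the choice of test. It needs no new data, visits or patients. The cost is fewer nominally significant results to report.

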### Safety assessment

2.15

Adverse reactions, symptoms and vital signs, and the results of routine physical examinations and complete blood analyses will be recorded at baseline prior to administration of the drug, at intermediate visits and at the final visit. Adverse events will be assessed throughout this clinical trial.

### Data management

2.16

Subject clinical trial data is collected using an electronic data capture (EDC) system. All data is entered into the e-CRF according to the e-CRF instructions provided by the sponsor. The sponsor or its agent performs verification with the supporting documentation for the completeness of the data. If data is missing or inconsistent, use the EDC system to resolve it with the principal in charge. The investigator shall digitally sign the locked e-CRF after verifying the entered data. Records of the identity of all subjects are kept confidential and subject identity is kept confidential even when the results of clinical trials are published. However, sponsors, monitors, IRB committees and directors of the KFDA involved in the study may view the subject's records for the purpose of monitoring, reviewing and managing the progress of the study. All information should be kept confidential and in place with confidentiality facilities and management standards. In addition, all documents related to clinical trials, such as electronic case records, shall be recorded and distinguished by subject identification code, not subject's name.

## Discussion

3

Afatinib is an available drug that is administered orally. It is an ErbB family blocker that, in comparison with the first-generation EGFR-TKIs, irreversibly and selectively blocks signaling from all homodimers and heterodimers formed by EGFR and by the erb-b2 receptor tyrosine kinase 2 (HER2/ERBB2), HER3/ERBB3, and HER4/ERBB4 receptors.^[13,14]^ Recently, three studies on the role of afatinib have been published: a combined analysis of LuxLung 3 and 6^[15]^ and analyses of LuxLung 7^[16]^ and LuxLung8.^[17]^ In LuxLung 3 and 6, afatinib showed superiority over the first-generation EGFR-TKIs: only afatinib among EGFR-TKIs improved the overall survival in comparison with the platinum-based chemo doublet. In LuxLung 7, afatinib was compared with gefitinib in a phase 2 B, open-label, randomized, controlled trial of EGFR mutation-positive NSCLC in treatment-naive patients and showed significant improvement in progression-free survival (PFS) and time-to-treatment failure. In LuxLung 8, afatinib was compared with erlotinib in a phase 3, open-label, randomized, controlled trial involving patients with a stage IIIB or IV squamous cell carcinoma who had progressed after at least four cycles of platinum-based chemotherapy and who had shown significant improvements in PFS and OS. Despite remarkable outcome results, patients receiving EGFR-TKIs usually developed secondary resistance after approximately 9 to 13 months (median PFS: 9–12 months) and showed major adverse events grade 3 or higher, including diarrhea, rash or acne, and stomatitis or mucositis.^[16–18]^

Complementary alternative medicine is becoming more popular in Korea for the treatment of patients with cancer because traditional Korean medicine may have synergistic effects when combined with chemotherapy or radiotherapy.^[19]^ One systematic review reported that herbal medicine may increase efficacy and reduce toxicity when taken in combination with EGFR-TKI by patients with advanced NSCLC.^[20]^ According to the previous study, HAD-B1 suppressed the growth of solid tumors as compared with the vehicle or the cisplatin-treated control group in an A549 cell xenograft mouse model.^[10]^ Based on this result, a well-designed, randomized, controlled trial is needed to identify the efficacy of HAD-B1 plus afatinib in the treatment of EGFR-positive patients with locally advanced or metastatic NSCLC who need afatinib therapy, which is the motivation for this trial. If this trial is successful, it should provide high-quality evidence for the efficacy and safety of using HAD-B1 plus afatinib for clinical treatment of patients with NSCLC. Our hypotheses are as follows: The use of HAD B1 should improve the efficacy of afatinib in the treatment of EGFR-positive patients with locally advanced or metastatic NSCLC and should reduce the toxicity associated with afatinib. Moreover, this trial may provide clinical evidence supporting and advancing the use of integrative cancer therapy in the treatment of patients with locally advanced or metastatic NSCLC.
